### Content and conduct of physician intervention

The MD control constituted a "usual care" condition. That is, there was no attempt to change or monitor whatever procedures were already in place in that practice for quality improvement and physician education with regard to BP control. No performance data were collected from these physicians, and no performance feedback was given.

The active MD intervention consisted of 3 main elements. The first element included 2 training modules provided as on-line continuing medical education (CME) courses. The first module addressed the JNC-7 guidelines and the second addressed lifestyle modification for BP control. The modules were available in 3 formats (streaming audio, PowerPoint slide show, and print version) so that each physician could choose the most convenient modality. Each module required approximately 45 minutes to complete, included a quiz that gave immediate feedback on the answers, and resulted in CME credit through the Duke CME office. All physicians completed the modules before the first group session of the patient intervention.

The second element was an evaluation and treatment algorithm that summarized the major guidelines set forth in JNC-7. The BP management algorithm–derived from the JNC-7 guidelines and formatted as a decision tree–was mass-produced in a color-coded, laminated pocket card (Additional file 1) and provided to each physician randomized to the active MD intervention. The algorithm directly informed the portion of the CPM data form that was completed by the MD (Additional file 2).

The third element was a CQI-type procedure involving assessment of CPMs and quarterly feedback to physicians on their adherence to guidelines, including those related to lifestyle counseling. At each clinic randomized to the MD intervention, the clinic staff and participating physician completed a single-page CPM data form every time an HIP participant (in either patient treatment group) had a clinic visit. A clinic nurse completed the top half of the form (BP at current and last clinic visit, comorbidities), and the MD completed the bottom half (current BP medications, actions taken during the visit, follow-up interval). In addition, data from non-study participants were collected on anonymous forms 1 day each month to increase sample sizes for feedback reports. In both cases, the form was attached to the billing encounter form to prompt MDs to complete it. These data were converted into quarterly feedback reports that indicated to each physician: 1) the proportion of hypertensive participants with adequately controlled BP for that quarter and the previous quarters; 2) the proportion not at goal who had medication adjustments at the visit; 3) the proportion that received lifestyle modification counseling; 4) the proportion without diabetes (DM) or chronic kidney disease (CKD) who were at goal BP and also the proportion prescribed a thiazide diuretic; 5) the proportion with DM and/or CKD who were at goal BP and also the proportion prescribed an angiotensin-converting enzyme inhibitor/angiotensin receptor blocker; and 6) comparisons with peer MDs for each category.

### Content and conduct of the patient intervention

#### Patient control

Participants randomized to the control group had an individual brief visit with an interventionist after randomization, during which they received advice and brochures on lifestyle modification for BP control consistent with JNC-7. At the end of the study (18 months), after the final data collection visit, participants in the control group were offered an abbreviated version of the active intervention, which consisted of 6 weekly group sessions to help them make lifestyle changes to control BP (wait-list control).

#### Active intervention: structure and content

The active patient intervention was based on key theoretical constructs developed to guide health behavior change efforts, and on practical applications from previous trials of lifestyle change and CVD risk reduction [24-26].

The patient intervention was conducted by 2 interventionists who served in this role in previous studies. Training for the interventionists was provided by behavioral scientists and nutritionists, and included training in intervention content, group facilitation, and motivational interviewing [20]. Ongoing quality assurance for intervention delivery was provided through retraining, observation, and feedback for the interventionists. The patient intervention consisted of 20 weekly sessions provided over approximately 6 months, during which the participants met in small groups (n = 10–15 per group) with an interventionist. All intervention sessions took place at or near the participants' clinic site, providing a familiar location for these sessions.

Specific behavior change strategies comprising the HIP patient intervention are listed in Table 3. The materials developed to deliver the patient intervention included a leader's guide and a participant manual featuring self-monitoring tools. The leader's guide provided a standardized framework and structure for each group session, as well as resource materials for session discussions. The participant manual provided the general format, outline, and worksheets for each session. It included information about diet and physical activity, and emphasized changing behaviors. This manual was intended to complement the group session process and content by serving as a workbook during the sessions and as a reference between sessions.

**Table 3 T3:** Behavioral change strategies of the HIP active intervention

**Strategy**	**Definition**
Frequent contact	Attend weekly sessions for 20 weeks.

Group interaction and social support	Sessions were highly interactive and minimally didactic; participants were encouraged to share experiences that led to patient modeling behavior; they also were encouraged to help each other solve problems.

Goal setting and self-monitoring	Emphasis placed on individual's ability to regulate his/her behavior by setting goals and monitoring progress towards the goals. Participants kept records of dietary intake, physical activity, and medication usage at least 3 days a week. Records were reviewed by the interventionist to provide feedback and encourage or support participant's behavior change.

Identification of barriers and problem-solving	Interventions were patient-centered; interventionist assisted participant in identifying his/her own barriers and generating solutions.

Motivational interviewing	Patient-centered counseling emphasized support of self-efficacy and optimism for change; included reflective listening, objective feedback, and respect.

HIP = Hypertension Improvement Project.

The study also employed volunteer community health advisors (CHAs) who were identified and recruited from the same communities as the target population. These "natural leaders" were trained to participate in all aspects of the patient intervention. They assisted the interventionists in conducting the group sessions and were asked to lead portions of the activities or discussion so that the intervention was delivered in conjunction with members of the community. The CHAs also made monthly calls during the 6 months while the intervention was delivered and during the 12 months after the intervention. The purpose of these calls was to provide one-on-one counseling to encourage participants to make or maintain behavior changes. The above-mentioned leader's guide was developed at the appropriate education level and with cultural sensitivity so that it could also be used to train the CHAs. The CHAs participated in a 20-hour training program consisting of 4 weekly sessions covering general information about hypertension, dietary and physical activity interventions for BP control, community resources, facilitation of group education sessions, practical guidelines for helping peers, listening skills, lifestyle behavior change techniques, and skills in stress management, problem-solving, and goal setting. Certification and on-going supervision were similar to that provided to the interventionists.

The CHAs served as familiar, non-authoritative resources for study participants, strengthening communication between the research group and the participants and providing additional social support. The intent is that the CHAs will have sufficient knowledge and skills to serve as ongoing resources in their communities and to help sustain the effects of the project after it is completed.

The outcomes were measured at the level of the patient, who was exposed to neither intervention, MD intervention alone, patient intervention alone, or both interventions. Overall, 8 practices (4 per treatment group), 32 physicians (4 per practice; 16 per treatment group), and 574 patients (289 control and 285 intervention) were enrolled (Figure 2).

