**Figure 2 F2:**
[figure not shown]
**Design of the HIP study**. MD = physician.

Within the practices, patient participants were individually randomized to the patient intervention or to usual care. The patient intervention occurred shortly after initiation of the physician intervention and consisted of a 6-month group-based behavioral intervention conducted by trained interventionists, followed by brief monthly phone counseling for 12 months from a community health advisor (CHA). Follow-up measurements were performed at 6 and 18 months following randomization.

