### Analysis plan

The data cleaning and analysis stage of the HIP trial has begun. The adequacy of randomization will be assessed by comparing the baseline characteristics of the 4 study groups. Chi-square tests will be used for categorical variables, and the analysis of variance will be used for continuous variables.

For the patient intervention groups only, various measures pertaining to adherence to the patient intervention and its impact on intermediate outcomes will be summarized. For example, for each cohort, the number of intervention sessions attended will be summarized. Similarly, changes in weight, diet, and exercise will be tabulated, and whether the mean changes equal zero will be determined.

For the main analysis of BP changes, results by group and cohort will first be summarized, and then tested for a cohort-by-group interaction. If this interaction is non-significant–suggesting that the intervention effects are similar across cohorts–summary results will be reported but will include cohort as a control variable in all models. For the continuous outcome of systolic BP, the main comparison will be derived from an analysis of covariance model that controls for cohort and baseline systolic BP. The primary hypotheses of interest will be the main effect of the patient intervention, the main effect of the physician intervention, and the patient-by-physician interaction. This last interaction assesses, for example, whether the patient and physician interventions have a separate impact on outcome or, alternatively, whether they act synergistically. For the categorical outcome of percentage of patients at goal, a similar strategy will be followed using logistic regression, and these analyses will also be stratified by whether the patient was at goal at baseline.

The analysis plan accounts for the correlations among the responses for individual patients, these correlations being induced by the nesting of time points within patients within physicians within practices. The analysis of variance paradigm will be used, accounting for the correlations among the 3 time points by separately analyzing the paired scores representing differences between baseline and 6 months and between baseline and 18 months. These comparisons can be preceded by a statistical test, such as Hotelling's T^2^, that takes explicit account of these correlations.

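### The listed correlation structure omits the session group, so the patient-effect standard error is understated if outcomes correlate within groups

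*Protocol article*

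**What the plan says.** All places are in the Protocol article.

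- **Unit of randomisation** (Methods and design, text after Figure 2): within practices, "patient participants were individually randomized to the patient intervention or to usual care".
- **Delivery in the intervention arm** (Active intervention: structure and content): there were weekly sessions over about six months, "during which the participants met in small groups". The same sentence gives the group size: participants "met in small groups (n = 10–15 per group) with an interventionist". Table 3 makes the group part of the treatment: "Sessions were highly interactive and minimally didactic; participants were encouraged to share experiences that led to patient modeling behavior". The staffing is also shared: "The patient intervention was conducted by 2 interventionists".
- **Delivery in the control arm** (Patient control): "Participants randomized to the control group had an individual brief visit with an interventionist after randomization". Controls are offered group sessions only after the final 18-month measurement.
- **Model** (Analysis plan): systolic pressure is analysed by analysis of covariance, controlling for cohort and baseline systolic pressure. The patient main effect is one of three primary hypotheses.
- **Correlations recognised** (Analysis plan): "these correlations being induced by the nesting of time points within patients within physicians within practices". The only technique described is separate analysis of change scores, optionally preceded by Hotelling's T², and this deals with the repeated time points.
- **Power** (Sample size and statistical power): clustering and covariate adjustment are assumed to roughly cancel, with no ICC given. About 340 completers are said to give about 80% power for main effects.

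**The concern.** Patients are randomised one by one, but those in the intervention arm are then treated in groups and controls are not. This is a partially nested design: clustering by session group exists in one arm only, at both 6 and 18 months. Members of a group share an interventionist, a room, peer modelling and joint problem solving, so some positive correlation of their outcomes is a natural expectation.

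The Analysis plan names its levels of nesting explicitly, and the session group is not among them. This is therefore a stated structure that lacks a level, not a detail left for a fuller document. If the within-group correlation is appreciable, the test of the patient effect rejects too often and its confidence interval is too narrow. That effect is a primary hypothesis and would inform decisions on whether to adopt the programme.

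**Working it through.** **1. The plan's own figure.** The text implies an effect size of 0.3 SD. Two-sided alpha of 0.05 is assumed, since the article states none. With 170 per arm, 0.3 / √(2/170) = 2.766, and power = Φ(2.766 − 1.960) = 79%. The stated figure of about 80% reproduces, but only with no net clustering penalty.

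**2. Number of groups.** There are 285 intervention patients. 285/15 = 19 and 285/10 = 28.5, so about 19 to 29 groups. Per practice, 285/8 = 35.6 patients make between 35.6/15 = 2.4 and 35.6/10 = 3.6 groups.

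**3. Variance of the patient effect.** With group size m and group ICC ρ, the intervention-arm variance is multiplied by DE = 1 + (m − 1)ρ and the control-arm variance by 1. With near-equal arms (285 and 289):

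- ratio of true to model-based standard error: f = √((1 + DE)/2)
- shortfall of the model-based standard error: 1 − 1/f
- actual two-sided type I error: 2(1 − Φ(1.96/f)); coverage of the nominal 95% interval is its complement.

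The documents give no ρ, so the values below are assumptions. For m = 12:

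| ρ | DE | f | Shortfall | Type I error |
|---|---|---|---|---|
| 0.01 | 1.11 | 1.03 | 3% | 5.6% |
| 0.02 | 1.22 | 1.05 | 5% | 6.3% |
| 0.05 | 1.55 | 1.13 | 11% | 8.3% |
| 0.10 | 2.10 | 1.25 | 20% | 11.5% |

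Over the stated range m = 10 to 15 at ρ = 0.05, f runs from 1.11 to 1.16 and type I error from 7.7% to 9.2%.

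**4. Does a practice main effect repair it?** A simulation used 8 practices, each with 3 groups of 12 intervention patients and 36 controls, a practice ICC of 0.01 and 4,000 replicates per setting. It fitted the stated model with and without practice fixed effects:

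| Group ICC | Stated model | With practice effects |
|---|---|---|
| 0 | 0.053 | 0.053 |
| 0.01 | 0.057 | 0.057 |
| 0.02 | 0.058 | 0.058 |
| 0.05 | 0.076 | 0.077 |
| 0.10 | 0.111 | 0.113 |

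Monte Carlo error is about √(0.05 × 0.95/4000) = 0.003. A practice main effect makes no practical difference, because it shifts both arms of a practice equally and leaves the group-to-group variation within the intervention arm untouched.

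**5. An opposing force.** Practice variance left in the residual of the stated model inflates the model-based standard error a little. The two effects cancel at ρ = (2/(1 − ρ_c) − 2)/(m − 1), where ρ_c is the practice ICC. With m = 12.5, the midpoint of the stated range, this is about 0.002 / 0.004 / 0.009 for ρ_c = 0.01 / 0.02 / 0.05.

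**6. Power.** At 340 completers, m = 12 and ρ = 0.05, power is Φ(2.766/1.129 − 1.960) = 69%. But 574 were enrolled. The plan's 400 enrolled for 340 completers implies 15% dropout, and the same rate gives 574 × 0.85 ≈ 488 completers, or 244 per arm. Power is then 91% with no group correlation and 81% to 85% at ρ = 0.05 over m = 10 to 15. At ρ = 0.10 it is 72% to 79%.

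**The case against.** A reader might infer that the plan treats intervention patients as independent. It does not: the Analysis plan says that nesting within physicians and practices is accounted for, although it names no method for those levels. What can be said is that one further level is missing from the list.

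A reader might also infer that the standard error is certainly too small. That depends on a group ICC which the article does not report. Several features could keep it low: two trained interventionists, a leader's guide that standardises sessions, and continuing observation and retraining. Attendance is listed as a challenge, so working groups may have been smaller than planned. At an ICC of 0.01 the effect is minor, and very small values could be offset by practice variance in the residual.

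Some ways of handling practice would capture the correlation if groups did not cross practices, which is plausible because sessions were held at or near each clinic. Examples are a random practice-by-arm term or practice-level robust variance, though with only 8 practices. The article names neither, so it cannot be assumed that they were intended or ruled out.

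These arguments make the size of the problem conditional. They do not supply the missing level, and the one model that is specified would not detect it.

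**Conclusion.** The point holds in conditional form. The stated correlation structure omits a level of clustering that the intervention itself creates, in one arm only. If the group ICC for change in systolic pressure is appreciably positive and no other term captures it, the stated model understates the standard error of the patient main effect. Over an assumed ICC of 0.01 to 0.10 with groups of 12, the shortfall is about 3% to 20% and the actual type I error about 5.6% to 11.5%. It is negligible at the low end and material from about 0.05.

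This rests on assumed ICC values, near-equal arms, two-sided 5% testing and groups of the stated size. The documents do not show that the bias occurred. Nor do they support calling the trial underpowered for this effect on these grounds: given the number enrolled, power stays above 80% at an ICC of 0.05 under the plan's implied effect size and dropout.

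**What to change.** In the Analysis plan section, add session group to the listed nesting and estimate the patient effect in one of two ways:

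- a partially nested mixed model, with a random session-group effect in the intervention arm only, controls as singletons, arm-specific residual variance and small-sample degrees of freedom (for example Satterthwaite), alongside the practice and physician terms; or
- cluster-robust inference with session groups as clusters and controls as singletons.

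Enrolment is complete, so group membership has to come from existing group-assignment or attendance records. Attendance is in the measurement schedule (Table 5), but the article does not say that group identity was recorded, so this needs checking. Keep patients who never attended in the group to which they were assigned, or treat them as singletons if none is recorded. Report the estimated group ICC with the result.

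The cost is modest: an added group variance, a separate residual variance by arm, possibly some retrieval of group records, and a slightly wider interval for the patient effect. No new measurement on patients is needed.

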### Physician measurements

Measurements specific to the physician intervention are described above. All physicians, regardless of treatment assignment, were asked to complete a baseline questionnaire concerning their demographics, education, and training–variables that are potential mediators of the effect of the physician intervention on BP control (Table 4). In addition, at entry, 6 months, and 18 months, all physicians were asked to complete a questionnaire in which they reported their practice patterns and habits. For example, providers reported the average amount of time spent discussing hypertension and lifestyle changes with patients, in addition to addressing barriers to, confidence in, and patient adherence to lifestyle modification counseling.

**Table 4 T4:** Baseline physician characteristics (N = 32)

**Characteristic**	**%***
Age, mean years (SD)	47.9 (9.9)

Female sex	34

African-American race	16

Family medicine specialty	53

Internal medicine specialty	47

Years since MD degree, mean (SD)	20.7 (10.0)

Patients with HTN	28.9

Very familiar with JNC guidelines	31

* Unless otherwise indicated.

HTN = hypertension; JNC = Joint National Committee on Prevention, Evaluation, Detection, and Treatment of High Blood Pressure; SD = standard deviation.

### Patient measurements

All study measurements obtained from participants were collected during face-to-face clinic visits by trained, certified study personnel who were blinded to intervention assignment. At each time point (baseline, 6- and 18-month follow-up), BP was measured according to JNC-7 guidelines (i.e., seated quietly with back supported and feet on the floor for 5 minutes prior, appropriate size cuff, arm bared and supported, no ingestion or smoking for 30 minutes prior) by an oscillometric blood pressure machine. At each study visit, average BP was defined as the averaging of duplicate measurements taken on each of 2 separate visits at least 1 week apart. BP control was defined based on JNC-7 guidelines: average systolic BP < 140 mm Hg and diastolic BP < 90 mm Hg for participants without renal disease or diabetes, and systolic BP < 130 mm Hg and diastolic BP < 80 mm Hg for participants with 1 or both of these conditions. Other measurements included weight/BMI, a dietary assessment using the Block Food Frequency Questionnaire [27], a blood sample obtained after an overnight fast, a 24-hour urine collection, an objective assessment of physical activity using a triaxial accelerometer [28], an assessment of medication adherence by self report, and psychosocial questionnaires. The measurement schedules for patients and physicians are shown in Table 5.

**Table 5 T5:** Measurement schedule

**Time/variable**	**Baseline**	**3 mo.**	**6 mo.**	**9 mo.**	**12 mo.**	**15 mo.**	**18 mo.**
**Physicians**							

Personal characteristics and training	**X**						

Practice habits (self-report)	**X**		**x**				**x**

Clinical performance measure (intervention group only)	**X**	**x**	**x**	**x**	**x**	**x**	**x**

